## Abstract

**Background:**

Latino men who have sex with men (MSM) experienced a 13% increase in HIV diagnoses from 2010 to 2014, more than any other racial/ethnic subgroup of MSM in the United States. If current HIV diagnoses rates persist, about one in four Latino MSM in the United States will be diagnosed with HIV during their lifetime. Although some efficacious HIV prevention interventions for Latino MSM exist, none have focused on couples. This paper describes the protocol of a randomized controlled trial (RCT) to test the preliminary efficacy of a couple-based HIV prevention intervention that is culturally tailored for Latino men and their same-sex partners.

**Methods:**

The RCT will determine the preliminary efficacy of Connecting Latinos en Pareja (CLP) to increase the proportion of anal sex acts that are HIV protected (i.e., anal sex acts in which condoms, pre-exposure prophylaxis (PrEP), treatment as prevention (TasP), or a combination thereof, are used to reduce risk of HIV transmission). CLP builds upon previous couple-based interventions with white and black MSM by incorporating biomedical prevention techniques, such as PrEP and TasP, implementing a framework responsive to the couple’s serostatus, and addressing the socio-cultural factors that influence HIV risk among Latino MSM. We also include input from community stakeholders, members of the target population, and a community advisory board as part of intervention development. Assessments will be conducted at baseline, and 3- and 6-months post-intervention to examine the intervention effects on outcomes (HIV-protected sex acts), and factors potentially mediating or moderating intervention effects.

**Discussion:**

This paper describes an innovative RCT that incorporates multiple HIV prevention techniques for Latino MSM in couples, regardless of serostatus. The ongoing involvement of community stakeholders, members of the target population, and a community advisory board is emphasized, and plans for widespread dissemination and application of findings into practice are discussed.

**Trial registration:**

Trial registration: NCT03048838. Registered on 3 February 2017.

**Electronic supplementary material:**

The online version of this article (10.1186/s13063-018-2582-y) contains supplementary material, which is available to authorized users.

## Background

Latinos, particularly Latino men who have sex with men (MSM), have been disproportionately affected by HIV infection. In 2014, 84% of all newly HIV-infected Latinos in the US were MSM [1], and current HIV surveillance data predict that, if current infection rates continue, one in four Latino MSM will be diagnosed with HIV in his lifetime [2]. Research suggests that experiences of stigma, discrimination, marginalization, sexual objectification, negative cultural perceptions of homosexuality, and cultural values such as “*familismo*” and “*machismo*” elevate vulnerability for HIV infection among Latino MSM [3].

Although efficacious interventions for Latino MSM have been developed [4, 5], the present intervention, *Connecting Latinos en Pareja* (CLP), is the only intervention developed specifically for Latino male couples, though it has yet to be rigorously and empirically evaluated. Findings from our formative study with Latino MSM suggest that the factors driving HIV risk for white male couples also operate among Latino male couples [6]. For instance, Latino men in male couples were more likely to report condomless anal sex and problematic alcohol use than those who were not in a relationship [6]. Developing and testing tailored interventions for Latino male couples is warranted to curb HIV infection among Latino MSM.

The present intervention, CLP, is an adaptation of a couple-based intervention for black male couples, *Connect ‘n Unite* [7]. CLP is novel in that it (1) integrates both biomedical prevention techniques (i.e., pre-exposure prophylaxis (PrEP) and treatment as prevention (TasP)) and psycho-educational skill building; (2) is adaptable for HIV prevention among both seroconcordant and serodiscordant couples; (3) employs an innovative algorithm for measuring HIV protection that goes beyond condom use as the sole indicator of HIV protection; and (4) is culturally tailored to Latino couples to address social, environmental, and contextual factors that intensify HIV risk in this population.

## Methods

### Theoretical underpinnings of CLP

Similar to CLP’s parent interventions, *Connect* and *Connect ‘n Unite*, CLP is grounded in social cognitive theory (SCT) and a relationship-oriented ecological framework [8, 9]. In concert with SCT, the content and activities utilized in CLP are designed to (1) provide information and knowledge to promote accurate risk appraisal; (2) build social and self-regulatory skills through problem solving, role plays, and other cognitive behavioral strategies; (3) increase self-efficacy to engage in HIV-protected sex and reduce risk behaviors; (4) increase positive outcome expectancies regarding HIV protection strategies; and (5) build and sustain social support networks for practicing HIV-protected sex. See Table 1 for constructs and measurements.

**Table 1 Tab1:** Constructs and measurement instruments for Connecting Latinos en Pareja (CLP), 2017

Construct	Assessment Instruments
Primary Outcome (last 3 months)	Risk Behavior Assessment (adapted to include PrEP and TasP) [24]
Proportion of HIV-protected anal sex acts (condom, PrEP, TasP) with main male partner in last 3 months	AACTG Adherence Measure [25]
Secondary Outcomes	
Use of HIV protection (condom, PrEP, TasP) with most recent casual partner	Self-reported viral load and missed dose count
Number of casual sex partners in the last 3 months, including female partners	Visual Analog Scale for medication adherence [26]
Sero-sorting and strategic positioning	Sero-sorting and Strategic Positioning Questionnaire [27]
Smoking, alcohol, and substance use	Substance Use Inventory [24, 27]
Social Cognitive Factors	
HIV protection methods outcome expectancy	Condom Use Expectancies Scale [28]
HIV protection methods self-efficacy	Condom Use Self-Efficacy Scale [29]
Social support	Multidimensional Scale of Perceived Social Support [30]
Relationship-Oriented Ecological Factors	
Relationship attributes (e.g., length of time in relationship, engagement in extra-dyadic relationships)	Relationship Attributes [27]
Intimate partner violence	Intimate Partner Violence Screening Tool for Gay and Bisexual Men [31]
Relationship satisfaction and support	Same-Gender Couples Scale [32]
Communication	Communication Patterns Questionnaire [33]
Sexual communication	Sexual Communication Questionnaire [34]
Sexual relationship power	Sexual Relationship Power Scale [35]
Sexual satisfaction	Sexual Satisfaction Scale [36]
HIV-related dyadic measures	HIV-Related Dyadic Measures [27]
Social, Environmental, and Other Factors	
Sociodemographic variables (i.e., age, gender, education, income)	Sociodemographic Questionnaire [37]
Childhood sexual abuse	Childhood Sexual Abuse Assessment [37]
Psychological symptoms	Brief Symptom Inventory (BSI) [38]
Religiosity	Santa Clara’s Strength of Religious Faith Scale [39]
Acculturation	SASH Brief Scale [26]
Experiences of discrimination	Everyday Discrimination Scale [25]
Heteronormative indicators	Conservative/Traditional Moral Views in Sexuality Questionnaire [24]Gender Ideology Scale [40]Internalized Homophobia Scale [41]
Service system involvement	Services Review [24]
Neighborhood environment & safety	Social/Physical Order/Disorder Questionnaire [42]

The relationship-oriented ecological perspective refines SCT constructs and incorporates contextual, multilevel dynamics that influence risk among intimate partners. The ontogenetic level focuses on each partner’s developmental history and personal attributes (e.g., histories of childhood sexual abuse) and SCT constructs (e.g., PrEP use outcome expectancies) [8, 9]. CLP prompts participants to examine how their past experiences influence their current sexual practices. The microsystem consists of structural factors that are part of the immediate intimate relationship context in which sexual activity and risk/protective behaviors occur [8, 9]. CLP’s activities target communication and negotiation skills related to sexual risk behaviors, protection, and pleasure, as well as sexual decision-making, power, and control. CLP also addresses how the use of alcohol and other substances impairs cognition, which may undermine negotiation and mutual decision-making. See SPIRIT 2013 checklist (Additional file 1) and Fig. 2 for all study protocols.

The “exolevel” refers to external factors impinging on the immediate setting by acting as stressors or buffers on the likelihood of engaging in particular behaviors [8, 9]. CLP aims to strengthen social support and peer norms for having HIV-protected sex and limiting the use of alcohol and/or other drugs in sexual contexts. The “macrosystem” encompasses broad cultural values and belief systems (e.g., the “man” is the penetrator; if you disclose your sexuality or HIV status, your family will reject you) and stereotypes of Latino men (e.g., hot, desirable lovers; sex objects in the sexual marketplace) [8, 9]. CLP prompts participants to examine how these cultural values, beliefs, and stereotypes influence the couple’s sexual practices [9]. It also helps to build internal resources and external social support networks to reverse the objectification, rejection, and/or disenfranchisement that have been linked to HIV-risk behaviors [10].

### Study aims

The present study is guided by two aims:

Aim 1:To finalize and pilot test the CLP and control interventions and assessment measures, and to conduct preparatory activities to launch the randomized control trial (RCT).

Aim 2:To conduct a RCT (*n* = 150 Latino male couples) to test whether participants assigned to CLP report a higher proportion of HIV-protected anal sex acts with their main partners than those assigned to an attention control intervention, and to preliminarily examine the potential mediators and moderators of the intervention effects.

### Overview of study design

We will test the preliminary efficacy of CLP using a RCT design with two arms – the experimental intervention, CLP, and an attention control condition, Wellness Promotion intervention, which uses an identical couple modality and is comparable in time and attention [7]. The study will follow a two-phase timeline that coincides with the study aims. During phase one, intervention manuals and assessment measures will be developed, pilot tested, refined, and finalized. During phase two, we will recruit a sample of Latino male couples (*n* = 150 couples) and conduct a RCT to test the efficacy of the treatment intervention. Study phases and related activities are outlined in Fig. 1.

**Fig. 1 Fig1:**
[figure not shown]
Study design schema for Connecting Latinos en Pareja (CLP), 2017

The study has been approved by the Institutional Review Boards of Temple University, the Philadelphia Department of Health, and the National Centers for HIV, Viral Hepatitis, STD, and TB Prevention’s project determination process. We have also obtained a certificate of confidentiality from the National Institute of Mental Health.

### Study sites

The primary assessment and project management activities will be conducted at Gay and Lesbian, Latino AIDS Education Initiative (GALAEI), a large Latino-serving community-based organization in North Philadelphia providing a range of services for LGBTQ Latinos, including HIV testing and prevention services, and services for people living with HIV. Recruitment and screening will be performed through community and internet venues. Intervention activities will be conducted at GALAEI, Temple University, and other safe spaces convenient to study participants.

### Community involvement and CAB

Active engagement of the host community has been identified as a ‘vital’ force in the implementation of successful, locally appropriate HIV prevention trials [11]. Throughout all phases of the study, input from the community and target population will inform the refinement and delivery of the intervention. During phase one of the study, we will convene a community advisory board (CAB) of 10 individuals, including key opinion leaders form the Latino MSM community, providers serving the health needs of Latino MSM, and community members. We will work closely with our community partners in identifying and selecting the CAB members to ensure that they are well-informed and able to provide the needed guidance.

Members of the CAB will be divided into two cohorts, each consisting of five members. Each cohort will participate in a CAB meeting once per year throughout the entire study duration. During phase one, the CAB will assist us in finalizing the interventions and assessments, identifying appropriate couples to participate in the refinement of the interventions, determining recruitment venues for the RCT, and other study-related activities. Two trained facilitators will present the goals, themes, key conceptual components, sample scenarios, role-plays, and key activities from the intervention sessions and solicit input from CAB members during audio-recorded sessions. The investigative team will audio-record the meetings and supplement them with transcribed meeting notes, then tag and group the information from each note by intervention content and activities. We will use this input to revise the interventions, while ensuring that we retain fidelity to the core components of the parent interventions.

Throughout phase two of the study (implementation of RCT), the CAB will convene and advise the investigative team on all aspects of the study, and will play a key role in reviewing ongoing study progress, developing plans to overcome challenges and handle adverse events, and interpreting and disseminating study findings. To date, CAB members’ feedback has been integrated into the refinement of study materials and has contributed to the formulation of a study logo and recruitment flyers.

### Couple pilot testing

To ensure that the interventions are culturally appropriate and relevant to the target population, phase one also involves a pilot test of the interventions and assessment materials with six male couples (in which at least one member of the dyad identifies as Latino/Hispanic). With the assistance of our CAB, GALAEI staff, and other community partners, we will identify 10 male couples that reflect the diversity of our future participants (e.g., concordant/discordant serostatus, racial/ethnic composition, age) and who are able to significantly contribute to the refinement of the intervention based on the initial interview. Of the 10 couples identified, six will be selected to pilot test the intervention, and four will act as alternates in case of attrition.

Once couples are recruited for pilot testing, a trained facilitator will administer the CAB-refined intervention sessions to three couples and couples will provide post-session feedback. Intervention sessions and review discussions will be audio-recorded and supplemented with transcribed notes; the facilitator will summarize the key themes. In addition to examining the intervention components (including activities and homework assignments) and reviewing language considerations, couples will provide input on logistics such as the structure of the intervention (e.g., length of time, frequency). The facilitator will group and summarize the material in a way that allows evaluation of the following:How comfortable were participants with the intervention content?What were the range and types of reactions to the specific content (e.g., communication and negotiation skills, HIV self-testing, PrEP, TasP, intimate partner violence, problematic alcohol use)?How did couple and relationship dynamics manifest throughout and affect the session?What are potential individual and dyad-level adverse reactions, if any?How well did the intervention relate to prominent issues among Latino male couples?How can the delivery style be enhanced with respect to cultural congruency and language use?

The team will incorporate refinements into the intervention based on the information provided and revise the session manuals accordingly. This process will be repeated with the remaining three couples, whose input will be used to make the final revisions to the sessions. The revised intervention will be presented to the members of our CAB, highlighting the revisions made. Once finalized, we will translate the manuals from Spanish to English. Couples who participate in this phase of the study will not be considered study participants, since they will serve in an advisory role, and any data collected from them will be used solely to refine the intervention, not to evaluate the intervention’s efficacy.

### Recruitment

We will recruit a sample of 150 male couples from community venues frequented by our study population (e.g., beaches, parks, gyms, coffee houses, clubs, community-based organizations, social clubs), internet venues and a study website, and online channels geared toward MSM (e.g. Grindr, Scruff, Jack’d). Across all venues, we will use methods such as (1) directly approaching men in community and internet venues, (2) making presentations at our community partners and special events, (3) obtaining referrals from community partners, (4) posting advertisements in selected internet and community venues, and (5) obtaining self-referrals or other referrals to recruit participants.

In both community and internet venues, trained bilingual staff will approach potential participants, describe the study, and obtain permission to screen for eligibility. In community venues, screening will be done electronically using smartphones or tablets; those engaged through internet venues will be asked to complete the formal screening via telephone or an online questionnaire.

Given that the study is couple-based, screening and eligibility determination will occur in two steps. First, the initial partner (Partner A) will complete the screening. He will be deemed ‘preliminarily eligible’ if he (1) meets demographic eligibility criteria (over 18 years old, identifies as a man who has sex with men, lives within the study area, identifies as Latino or reports having a partner who identifies as such) and (2) reports either two instances of HIV-unprotected anal sex within the relationship or at least one instance of HIV-unprotected anal sex with a male partner outside the relationship in the last 90 days. Operationalization of ‘HIV-protected’ and ‘HIV-unprotected’ anal sex acts will vary based on the couple’s serostatus, and will be determined by reported use of condoms, PrEP, and viral suppression (for HIV-positive individuals), or a combination thereof. If Partner A is eligible, the automated screening program will ask him to invite Partner B to complete the screening through the study website, telephone, or in person. Final eligibility determination of the couple will occur when Partner B completes the screener and the program determines whether or not the couple is eligible based on their linked data.

### Randomization to conditions

A computerized randomization program will be used to randomly assign couples to the treatment conditions with equal probability at the first study visit while they are completing the baseline assessment. Including both the baseline assessment and delivery of the first intervention session at the initial study visit minimizes potential biases in treatment effect estimates, due to differential attrition between randomization and the first session. It also ensures that all enrolled couples receive at least one intervention session.

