### Measures

Assessments will occur at baseline and 3 and 6 months post-intervention; assessments will be interviewer-administered and conducted at the individual level to ensure confidentiality.

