Sexual behavior will be assessed separately for main male partners and casual male and female partners, if applicable. We will classify 100% condom use for anal insertive or anal receptive with main partner in the last 3 months as HIV-protected acts. For participants who report less than 100% condom use, we will assess whether those sex acts that were not protected by condoms were protected by PrEP (for HIV-negative seroconcordant or serodiscordant couples) or TasP (for HIV-positive seroconcordant or serodiscordant couples). Although the intervention is delivered at the dyad level, sexual risk will be assessed at the individual level, given the possibility that some couples who completed the intervention may not be together at either follow-up. Thus, assessments of sexual risk with primary partners will measure sexual behavior with participants’ current primary partner, whether or not this is the same partner who completed the intervention.

Among participants who report viral suppression or use of PrEP, medication adherence will be assessed by multiple measures to confirm the high probability of maintained viral suppression or PrEP protection, respectively, across those sex acts not protected by condom use. These measures include missed dose counts, a visual analog scale [12], and validated AIDS Clinical Trials Group adherence measures [13]. Although these assessments are based on self-report rather than biomarkers (i.e., viral load tests to confirm sustained viral suppression, blood tests to assess antiretroviral adherence), the proposed algorithm provides a comprehensive conceptualization of HIV protection that incorporates currently available prevention approaches.

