### Data analysis

Initial data analysis tasks will involve univariate and bivariate statistics to characterize the sample and review the distributional properties of measures across treatment arms. To evaluate the efficacy of the intervention, we will use random effect models and/or generalized estimating equations (GEE) modeling 6-month follow-up differences, adjusting for characteristics at baseline, 3-months, and treatment arm in order to increase statistical precision. GEE models will consistently be used in cases where unobserved heterogeneity invalidates the application of random effect models. Additional covariates will be included as indicated by comparison of baseline differences and variables of theoretical importance (e.g., serostatus concordance). We will also explicitly test baseline × treatment interactions. We expect to model our main outcome as a continuous variable, but based upon examination of pilot data, some adjustment for interval censoring (i.e., considerable proportions reporting condom use on all or no occasions) may be required in order to meet distributional assumptions.

Following evaluation of Aim 2, we will perform a set of exploratory analyses to develop dyadic models for sero-discordant couples in which partners are not exchangeable in terms of risk [15]. We will also explore factors associated with the magnitude of treatment effects (i.e., potential moderators) as well as potential mediators. Effect modification will be evaluated directly through random effects models or as multiplicative composites in GEE models. Hypothesis testing will implement an intention-to-treat approach. We will employ GEE to account for the non-independence in measures arising from (1) “autocorrelation”, due to repeated measures with the same person, and (2) “intraclass correlation”, arising from partners in a dyad who are reporting on behaviors conjoint within that dyad.

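### Couples are randomised before the baseline interviews are finished; the single-visit rationale does not need this, and baseline is open to arm-related reporting unless the arm stays hidden

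*Protocol article*

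**What the plan says.** Under Randomization to conditions, a computerised program will "randomly assign couples to the treatment conditions with equal probability at the first study visit while they are completing the baseline assessment". The reason follows: "Including both the baseline assessment and delivery of the first intervention session at the initial study visit minimizes potential biases in treatment effect estimates", because couples are then not lost at different rates between assignment and session one. The section adds that every enrolled couple will thereby receive at least one session.

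Under Measures, "assessments will be interviewer-administered and conducted at the individual level to ensure confidentiality". Under Primary outcome: HIV-protected acts, the article says of the adherence and viral-suppression measures that "these assessments are based on self-report rather than biomarkers".

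Data analysis uses baseline in three ways:
- The efficacy models compare the arms at 6 months, "adjusting for characteristics at baseline, 3-months, and treatment arm in order to increase statistical precision".
- "Additional covariates will be included as indicated by comparison of baseline differences and variables of theoretical importance".
- Baseline-by-treatment interactions are to be tested explicitly.

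The same section commits hypothesis testing to intention to treat.

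**The concern.** A baseline measurement earns its place in the analysis because assignment cannot have affected it. The usual safeguard is to finish baseline first and assign afterwards. Here the stated order is different: assignment falls inside the baseline assessment. The two men in a couple are interviewed separately and need not finish together, so some answers from one or both can be given after the couple's arm has been set.

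Two things are at stake. If the arm becomes known before the interviews end, probing or answering on sensitive behaviour could differ by arm, and all three uses of baseline would inherit that difference. Separately, and whether or not the arm is known, the interval between randomisation and session one now contains the rest of the baseline interview. A couple that stops in that interval counts as randomised, with an incomplete baseline and no session.

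**Working it through.** No figure in the article depends on this point, so there is none to reproduce. The check sets the sections side by side and then works out the direction of any bias.

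**1. Order of events.** From Randomization to conditions, the first visit runs: baseline starts, assignment is made, baseline ends, session one is delivered. The article does not say that baseline is complete or locked before assignment. It also does not say when the interviewer or the couple learns the arm.

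**2. The stated reason against that order.** The reason concerns loss between assignment and session one.
- With assignment during baseline, that interval is the remainder of both interviews plus any wait for the session.
- With assignment after both baselines, at the same visit, it is the wait alone.

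The single visit delivers the benefit and early assignment adds nothing to it. Early assignment also weakens the assurance that every enrolled couple gets a session, because a couple can leave after assignment and before session one. Under intention to treat that couple remains in the comparison.

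**3. Effect of a reporting shift on the adjusted estimate.** Let *Y* be the 6-month outcome, *X* a self-reported baseline covariate, and β its slope in the model. The adjusted effect is

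(Ȳ_CLP − Ȳ_control) − β × (X̄_CLP − X̄_control).

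If *X* is unaffected by assignment, randomisation makes the expected difference in *X* zero. If knowledge of the arm shifts reported *X* by δ in CLP relative to control, the expected difference is δ, and

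bias = −β × δ.

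This treats the shift as confined to baseline reports and β as otherwise unchanged. With β positive, the bias runs opposite to the shift. If CLP couples over-report protection at baseline, CLP looks worse; if they under-report it, CLP looks better. If the arm is hidden until both interviews end, δ = 0 and the bias is zero.

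**4. The other two uses.**
- Covariate selection: a nonzero δ appears as a baseline difference, so choosing covariates by comparing baseline differences favours the affected variable.
- Interaction: a uniform δ leaves the difference in slopes alone but moves the estimated effect at any given baseline value. A shift that varies with the true baseline level changes the interaction term itself.

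**5. Size.** The article gives neither δ nor β. The autocorrelation of 0.15 under Power analysis is a design input and is not stated to be a slope in the efficacy model. No magnitude can be supported.

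**The case against.** The strongest reply is that generating an allocation is not the same as revealing it. A list prepared in advance exists before any baseline and does no harm while concealed. The article says when the program assigns but not who sees the result or when, and a condensed article may leave that to the full protocol. This stands. A reader might infer that interviewers or couples know the arm while answering; the document does not say so.

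Three related inferences also lack support:
- A reader might suppose that the interviewing staff are preparing session one. Assessments are given by interviewers and sessions by a trained facilitator, and the article does not say that these are the same people.
- A reader might take the baseline interview as the source of couple serostatus. Under Recruitment, serostatus already enters the eligibility classification at screening, from both partners' linked data.
- A reader might take baseline sexual behaviour to be the main covariate. Data analysis refers only to characteristics at baseline.

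It can also be said that no session content has been delivered at this stage, that both programmes have the same length and couple format, that moderation is labelled exploratory, and that intention to treat and the missing-data sensitivity analyses deal with early leavers. These points limit the likely harm. They do not supply a reason for assigning early. The analysis commitments handle couples lost after randomisation, whereas later assignment would keep those who leave during baseline from being randomised at all.

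**Conclusion.** The point holds as a weakness in the stated order of procedures, not as a demonstrated bias. Assignment during baseline is what the article prescribes. It gains nothing for the reason given, lengthens the interval that reason seeks to shorten, and allows a couple to be randomised without a complete baseline or a session. That part does not depend on who knows the arm.

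The reporting part is conditional. It is nil if the arm is hidden until both interviews end. Otherwise the adjusted effect is biased by −β × δ, opposite in sign to the shift when β is positive, and the covariate selection and interaction tests are open to distortion. The size is not quantifiable from the document. The conclusion assumes that the article's wording on timing describes what is done at the visit.

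**What to change.** Set the computerised program to generate and release a couple's allocation only after both partners' baseline forms are complete and locked, at the same first visit, and then begin session one. State in the protocol that neither the interviewers nor the couple can see the arm before the lock. If this is already the practice, correct the sentence under Randomization to conditions to say so.

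Randomisation is already computerised and data capture electronic, so this is a change of setting. Sample size, number of visits and the same-visit first session are unaffected. The downside is at most a short wait between the end of the interviews and session one. The article reports that recruitment is under way, so the change would apply to couples still to be enrolled, and the date on which it takes effect should be recorded.
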